
### Study oversight and quality assurance

2.16

The study team will establish an expert steering committee to provide guidance on issues encountered during the study.An investigator's study manual will be prepared, and relevant standard operating procedures (SOPs) will be developed to ensure the objectivity of clinical data collection.Before the start of the study, all study personnel will receive training and undergo a consistency assessment.A quality control (QC) team will be established. A quality monitor will periodically inspect the study conduct and hold regular meetings to discuss specific issues arising from the work.A data management center will be established, and operational rules for data management will be formulated to ensure data accuracy.Quality Control for Traditional Chinese Medicine (TCM) Syndrome Assessment1) Standardised training and assessment content: All investigators responsible for syndrome differentiation at each sub-centre will receive unified central remote training. Before formally participating in subject screening and enrolment, they are required to pass a test consisting of 10 standardised case scenarios, in which their syndrome differentiation and syndrome score results must achieve a Kappa coefficient and intraclass correlation coefficient (ICC) of ≥0.80 against the gold standard (established by two senior TCM attending physicians). 2) Discrepancy resolution mechanism: i) Internal preliminary review (at the sub-centre level): Each sub-centre must be staffed by at least two certified investigators (primary investigator and co-investigator). When the initial assessing investigator has doubts regarding the syndrome type or the assignment of syndrome scores, an immediate two-person independent (blinded) re-assessment must be initiated. If the two agree, the consensus is adopted; if they disagree and cannot reach a consensus after internal discussion, the case is escalated to secondary adjudication. ii) Central arbitration (at the expert panel level): For cases that cannot be resolved at the sub-centre level, the complete case documentation must be uploaded to the data management system within 24 h and submitted to the Central Adjudication Committee (composed of three senior TCM attending physicians not involved in the clinical trial at that centre). A majority voting rule (at least 2/3 of votes) will be applied for rapid adjudication. iii) Regular calibration and feedback: The Central Adjudication Committee will summarise all “disputed cases” and “adjudication outcomes” on a monthly basis, revise the Investigator's Manual accordingly, and provide targeted re-training to the relevant sub-centres, so as to reduce the occurrence of similar disputes at the source. 3) Blinded assessment: The Clinical Research Associate (CRA) will randomly select tongue-pulse photographs and syndrome scales from 5% of enrolled cases at each centre, and conduct a cross-centre retrospective consistency review. Should the Kappa coefficient and ICC at any sub-centre fall below the above thresholds, or should the rate of disputes be excessively high, we will suspend enrolment at that centre until re-training has been completed and the test has been passed.

### Missing data and protocol deviation handling

2.17

For the primary endpoint, the MMRM provides valid estimates under the missing-at-random (MAR) assumption using all available observed data. To test the robustness of the MAR assumption, two sensitivity analyses will be performed: (i) complete-case analysis, restricted to patients who completed the full 24-week follow-up; and (ii) worst-case scenario analysis, in which missing values in the SXYX group are imputed with the minimum observed value and those in the placebo group with the maximum observed value. For secondary endpoints with a missing rate >10%, multiple imputation (MI) using a chained-equation approach will be applied, with the imputation model including all covariates and outcome variables. For patients who meet the mITT criteria (i.e., have received at least one dose of the study drug and have at least one post-baseline CPET assessment), if they experience any of the following events—(i) premature discontinuation of the study drug, (ii) receipt of rescue therapy for worsening heart failure (e.g., intravenous diuretics), (iii) hospitalisation for any reason, (iiii) Medication adjustments due to various reasons, or (iiiii) inability to complete CPET—they will still be retained in the mITT set (in accordance with the intention-to-treat principle), but will be excluded from the per-protocol set for sensitivity analyses. All protocol deviations will be summarised and listed by treatment group, and submitted to the Data Monitoring Committee for review in the final report.

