##### Background therapy

2.11.3.1

Standard Western medical treatment will be provided according to the *2024 Chinese Guidelines for the Diagnosis and Treatment of Heart Failure* (28), and a set of principles for medication management and adjustment will be formulated.
(1)Principle of stable baseline medicationBefore randomisation, all subjects are required to undergo a stabilisation period of at least 2–4 weeks on guideline-directed medical therapy (GDMT), and the medication regimen at the end of this stabilisation period is defined as the “baseline treatment regimen”. Criteria for medication stability are: (i) no arbitrary change in drug class; (ii) the dosage of any individual drug should not fluctuate by more than 25% relative to the recent stable regimen.(2)Principles for adjustment of drug class and dosageThroughout the trial, investigators are strongly encouraged to maintain the baseline medication regimen unchanged. If the initiation of any new core heart failure therapy, particularly sodium–glucose co-transporter 2 inhibitors (SGLT2i), angiotensin receptor–neprilysin inhibitors (ARNI), and mineralocorticoid receptor antagonists (MRA), becomes necessary due to newly emerging serious clinical indications, approval must be obtained from the principal investigator (PI) of the participating centre, and the event must be documented as a major protocol deviation, which will be excluded in sensitivity analyses performed in the final statistical analysis. Loop diuretic doses may be adjusted at any time to manage volume status; however, if the diuretic dose increases by >50% from baseline and persists for more than 72 h, this will be classified as a “major medication adjustment”. For medications used to treat comorbidities, the drug class and dosage should remain unchanged in the absence of safety concerns; if adjustment is truly necessary, it should be strictly in accordance with clinical guidelines, and the adjustment should be recorded.(3)Criteria for initiation of rescue therapyTo ensure patient safety while maintaining the integrity of the modified intention-to-treat (mITT) analysis set, rescue therapy should be initiated if any of the following criteria are met: (i) worsening signs or symptoms of heart failure requiring temporary intravenous diuretic use or hospitalisation for heart failure; (ii) an increase in loop diuretic dose of ≥30% from baseline at two consecutive visits, or a single dose up-titration of ≥100%; (iii) sustained weight gain of ≥2 kg within 7 days after increasing the oral diuretic dose; (iiii) symptomatic hypotension (systolic blood pressure <90 mmHg) or a decline in estimated glomerular filtration rate (eGFR) of >30% from baseline, induced by standard pharmacotherapy.(4)Documentation standards for medication adjustmentsAt each study visit (screening, baseline, weeks 4, 8, 12, 18, and 24), all concomitant medications and any adjustments must be recorded completely and in detail in the case report form (CRF). The documentation should include the medication name, dose, frequency, start and end dates of administration, and the reason for the adjustment.(5)Pre-specified subgroup stratification and statistical adjustment strategyRandomisation stratification factor: baseline use of sodium–glucose co-transporter 2 inhibitors (SGLT2i) will be added as a mandatory stratification factor at the randomisation stage (stratified as “used” vs. “not used”). Subgroup analyses: pre-specified subgroup analyses will be performed to examine the treatment effect of the study intervention on peak oxygen consumption (peak VO_2_), according to baseline exposure to SGLT2i and glucagon-like peptide-1 receptor agonists (GLP-1 RAs). Statistical adjustment plan: to control for residual confounding, major medication adjustments and cumulative diuretic exposure (uniformly converted to furosemide equivalent doses) will be included as time-varying covariates in the mixed-effects model for the primary endpoint. In addition, a per-protocol sensitivity analysis will be conducted, excluding subjects with major protocol violations.

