### Investigational drug management

2.12

The study team will initially distribute the investigational drug to each center according to its expected enrollment schedule and record the distribution. Subsequent shipments will be dynamically adjusted based on actual enrollment progress, and an inventory alert threshold will be set (e.g., when the stock falls below a 2-week supply) to prevent drug shortages. In this double-blind trial, the site drug administrator at each study center will be responsible for drug dispensing and patient instruction on proper use. The drug packaging and labeling comply with blinding and randomization requirements, and measures will be taken to ensure the drug does not deteriorate during storage and transportation. After the trial is completed, the site drug administrator will collect and count the remaining drug and return it to the study team.

Medication adherence will be calculated as (actual dose taken ÷ expected dose) × 100%. Adherence between 80% and 120% is considered good. The actual dose taken is calculated as: dispensed amount − returned amount − lost amount. For patients with poor adherence, the reasons should be identified and documented.

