### Statistical analysis

2.18

Statistical analyses will be performed using SPSS Statistics 32.0 (IBM Corp., Armonk, NY, USA) and R 4.2 (for mixed models). Three analysis populations are defined: (i) the modified intention-to-treat (mITT) set, comprising all randomized patients who received at least one dose of the study drug and had at least one post-baseline primary efficacy assessment—this serves as the primary analysis set; (ii) the per-protocol set (PPS), including patients who completed the 24-week trial without major protocol deviations, used for sensitivity analyses; and (iii) the safety set (SS), including all patients who received at least one dose of the study drug, used for safety analyses. Baseline and descriptive analyses: Baseline demographic and clinical characteristics (including age, sex, BMI, aetiology of heart failure, LVEF, NT-proBNP, SGLT2i use rate, etc.) will be compared between the two groups using independent-samples *t*-tests for continuous variables with normal distribution, Mann–Whitney *U* tests for continuous variables with non-normal distribution, or chi-square tests for categorical variables, in order to describe the balance after randomization. For safety analyses, comparisons of the incidence of adverse events between groups will also be performed using chi-square tests or Fisher's exact test. Primary endpoint analysis: The change in peak VO_2_ from baseline to week 24 is designated as the sole primary efficacy endpoint (week 12 change is reclassified as a key secondary endpoint). The primary analysis will be performed using a mixed-effects model for repeated measures (MMRM) rather than ANCOVA, with fixed effects including treatment group, visit (baseline, week 12, week 24), treatment-by-visit interaction, baseline peak VO_2_, baseline SGLT2 inhibitor use (yes/no), and study center. The MMRM was chosen because it uses all available longitudinal data and accounts for the correlation between repeated measurements within each subject, whereas ANCOVA would be limited to a single post-baseline time point and would not adequately handle the repeated-measure structure. Subject is included as a random effect (random intercept). The treatment effect will be reported as adjusted least-squares mean difference with 95% confidence intervals. Secondary endpoint analysis: Key secondary endpoints (including change in peak VO_2_ at week 12, NT-proBNP, 6-minute walk test, and NYHA functional class) will be analyzed using the same MMRM for continuous variables or logistic regression for categorical variables (with NYHA class dichotomized as improvement ≥1 grade vs. no improvement). To control type I error inflation due to multiplicity, a fixed-sequence testing procedure is prespecified: formal hypothesis testing for these four key secondary endpoints will proceed only if the primary endpoint (week 24 peak VO_2_) is statistically significant (*P* < 0.05), in the following order: ① week 12 peak VO_2_ change → ② NT-proBNP → ③ 6MWT → ④ NYHA class improvement (≥1 grade). All other secondary endpoints (including echocardiographic parameters, TCM syndrome score, individual symptoms/signs, EQ-5D, and coagulation function) are designated as exploratory/supportive endpoints, for which only descriptive statistics and unadjusted *P*-values will be reported; between-group comparisons for these exploratory endpoints will be performed using *t*-tests or Mann–Whitney *U* tests as appropriate, with unadjusted *P*-values provided for descriptive reference only, explicitly labelled as hypothesis-generating and not subject to formal inferential conclusions; hence, no multiplicity adjustment is applied to them. Center heterogeneity: Study center is included as a fixed effect in all MMRM models to account for potential variations in CPET execution, background care, and baseline characteristics across sites, ensuring robustness of the pooled treatment estimate.

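### Section 2.17 drops rescued, hospitalised or medication-adjusted patients from the per-protocol set, while 2.18 and 2.11.3.1 drop only major deviations; membership is contradictory and, under 2.17, related to outcome

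*Protocol article*

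**What the plan says.** Section 2.17 lists five events after which a patient stays in the mITT set "but will be excluded from the per-protocol set for sensitivity analyses". The first is early discontinuation of study drug. The next two are "receipt of rescue therapy for worsening heart failure (e.g., intravenous diuretics), (iii) hospitalisation for any reason". The last two are "Medication adjustments due to various reasons, or (iiiii) inability to complete CPET". The medication item has no threshold of size, drug class or duration.

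Section 2.18 describes "the per-protocol set (PPS), including patients who completed the 24-week trial without major protocol deviations, used for sensitivity analyses". Section 2.11.3.1, item (5), says the same in substance: "a per-protocol sensitivity analysis will be conducted, excluding subjects with major protocol violations".

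On background drugs, 2.11.3.1 item (2) states: "Loop diuretic doses may be adjusted at any time to manage volume status". It reserves the label of major medication adjustment for a diuretic increase above 50% that lasts more than 72 h. It lets drugs for comorbidities be changed where truly necessary, provided the change is recorded. The one medication event that it says must be documented as a major protocol deviation is the start of a new core heart failure therapy.

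Section 2.12 defines good adherence as 80–120% and adds: "For patients with poor adherence, the reasons should be identified and documented". Section 2.15 has a blind review meeting settle the analysis populations before unblinding.

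**The concern.** The per-protocol analysis is named in three sections as a check on the primary result, so its membership should follow from the text. It does not: the two rules place the same patient in different sets.

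The wider rule also has a substantive problem. Rescue for worsening heart failure and heart failure admission occur after randomisation and reflect the disease under treatment. Dropping patients for them tends to remove those who did badly, and more of them in whichever arm does worse. A per-protocol estimate built this way can differ from the mITT estimate, or agree with it, for reasons unrelated to whether the protocol was followed.

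The plan also handles related events in two ways. Section 2.11.3.1 keeps patients with major medication adjustments in the primary model and adjusts for those events as time-varying covariates. Section 2.17 removes patients from the per-protocol set for any adjustment at all.

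**Working it through.** **Step 1: apply both rules to the same patients.** Each patient takes all study drug, completes 24 weeks and has a week-24 CPET.

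| Event during follow-up | 2.18 and 2.11.3.1 | 2.17 |
|---|---|---|
| One small permitted loop diuretic change | in | out |
| Necessary, recorded change to a comorbidity drug | in | out |
| Short admission unrelated to heart failure | in | out |
| Start of a new core heart failure therapy | out (major deviation) | out |

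Early discontinuation and a missed week-24 CPET may overlap with 2.18's requirement to complete the trial. The first three rows do not.

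**Step 2: the plan's own figures (2.2).** σ² = (4.8² + 4.2²)/2 = 20.34, so σ = 4.51. n per group = 2 × (1.96 + 1.282)² × 20.34 / 2.7² = 58.65, rounded up to 59; 59/0.8 = 73.75, rounded up to 74 per group and 148 in total. These reproduce and are not in dispute.

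**Step 3: how far selection could move the estimate.** The documents give no rates of rescue, admission or medication change, so this is an illustration. Assumptions: week-24 change is normal with SD 4.51 in both arms (an SD that the plan took from peak VO₂ levels, not changes); arm means are 0 and 2.7; a fraction f of patients below a cut-off c is removed and nobody above it. With a = (c − μ)/σ, the mean of those kept is

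μ + σ · f·φ(a) / (1 − f·Φ(a)).

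With c at the placebo 10th percentile, c = −5.78, so a = −1.282 for placebo and −1.880 for SXYX.

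- f = 1: placebo 4.51 × 0.1755/0.900 = 0.88; SXYX 2.7 + 4.51 × 0.0681/0.970 = 3.02; difference 2.14.
- f = 0.5: placebo 0.5 × 4.51 × 0.1755/0.950 = 0.42; SXYX 2.7 + 0.5 × 4.51 × 0.0681/0.985 = 2.86; difference 2.44.

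| Cut-off (placebo percentile) | Half removed | All removed | Kept if all removed, placebo / SXYX |
|---|---|---|---|
| 10th | 2.44 (10% smaller) | 2.14 (21% smaller) | 90% / 97% |
| 20th | 2.33 (14% smaller) | 1.81 (33% smaller) | 80% / 93% |
| 30th | 2.29 (15% smaller) | 1.56 (42% smaller) | 70% / 87% |

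A simulation with a gradual link (20–40% event probability at the placebo mean, higher for worse change) gave about 2.3 to 2.6, with unequal exclusions, for example 33% placebo against 23% SXYX. With no true effect, that mechanism produced no bias.

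**Step 4: loss of size.** If 10%, 30% or 50% of the 59 planned completers per group are also removed (assumed rates), about 53, 41 or 30 remain. Power for 2.7 falls from 90% to about 87%, 78% or 63%.

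**The case against.** The strongest reply is that 2.18 leaves the term major deviation open and that 2.17, whose title covers deviation handling, supplies the working list. Section 2.11.3.1 names one medication event as a major deviation without saying it is the only one. This narrows the conflict: 2.18 and 2.11.3.1 state one rule, so there are two rules, not three. It does not remove the conflict. A change that 2.11.3.1 expressly permits, and that falls below its own threshold for major, cannot also be a major deviation.

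It is also fair that the per-protocol set serves only sensitivity analysis. The mITT, complete-case and worst-case analyses do not depend on it, and the sets are fixed blind to allocation. Blind review prevents a choice made with knowledge of allocation. It does not remove selection on outcome-related events, and it leaves the meeting to choose between two written rules.

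Three stronger readings are tempting and are not supported:

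- A reader might infer that patients who hardly took the granules always stay in the set. Section 2.6(3) makes poor compliance with inability to complete treatment or assessments a discontinuation criterion, which leads out of the set. Neither rule cites the 80–120% range, but a numeric cut-off may properly sit in a statistical analysis plan.
- A reader might infer that starting a new core heart failure therapy is prohibited. Section 2.11.3.1 allows it with approval and has it recorded as a major deviation.
- A reader might infer that the plan already treats rescue or admission as intercurrent events. Section 2.10.2 applies that framework only to emergency unblinding.

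**Conclusion.** The contradiction stands on the text alone and needs no assumed rates: 2.17 on one side and 2.18 with 2.11.3.1 on the other give different per-protocol sets. That 2.17 selects on events related to outcome also stands, through rescue and heart failure admission.

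The size is unknown. On the stated assumptions, a true difference of 2.7 mL/kg/min would appear as 2.44 to 2.29 if half of the patients below the cut-offs are removed, and as 2.14 to 1.56 if all are. A reader might take the 21–42% loss as the expected distortion. It is an extreme case, because it needs every patient below a cut-off to have an excluding event and nobody above it, and nothing in the documents supports so sharp a link. The direction in practice also depends on the mechanism. Nor does it follow that the trial's result could not be interpreted, since the primary analysis uses the mITT set. This is worth correcting, but the consequence is confined to a sensitivity analysis.

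**What to change.** Before the blind review meeting:

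1. Use one per-protocol definition, based on major protocol deviations, in 2.11.3.1, 2.17 and 2.18.
2. In 2.17, remove rescue therapy, hospitalisation and permitted medication adjustments as automatic exclusions.
3. Extend the intercurrent-event handling that 2.10.2 now gives only to emergency unblinding to these events.
4. Use the adherence range already defined in 2.12 as the study-drug criterion.

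The medication statements in 2.11.3.1 and 2.17 must be reconciled for analysis purposes; no clinical rule needs to change.

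The cost is protocol wording. The downside is that the per-protocol set will include patients whose background drugs changed. Some outcome-related selection also remains, because starts of new core heart failure therapy stay major deviations and may themselves follow clinical worsening.

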### Statistical analysis

2.18

Statistical analyses will be performed using SPSS Statistics 32.0 (IBM Corp., Armonk, NY, USA) and R 4.2 (for mixed models). Three analysis populations are defined: (i) the modified intention-to-treat (mITT) set, comprising all randomized patients who received at least one dose of the study drug and had at least one post-baseline primary efficacy assessment—this serves as the primary analysis set; (ii) the per-protocol set (PPS), including patients who completed the 24-week trial without major protocol deviations, used for sensitivity analyses; and (iii) the safety set (SS), including all patients who received at least one dose of the study drug, used for safety analyses. Baseline and descriptive analyses: Baseline demographic and clinical characteristics (including age, sex, BMI, aetiology of heart failure, LVEF, NT-proBNP, SGLT2i use rate, etc.) will be compared between the two groups using independent-samples *t*-tests for continuous variables with normal distribution, Mann–Whitney *U* tests for continuous variables with non-normal distribution, or chi-square tests for categorical variables, in order to describe the balance after randomization. For safety analyses, comparisons of the incidence of adverse events between groups will also be performed using chi-square tests or Fisher's exact test. Primary endpoint analysis: The change in peak VO_2_ from baseline to week 24 is designated as the sole primary efficacy endpoint (week 12 change is reclassified as a key secondary endpoint). The primary analysis will be performed using a mixed-effects model for repeated measures (MMRM) rather than ANCOVA, with fixed effects including treatment group, visit (baseline, week 12, week 24), treatment-by-visit interaction, baseline peak VO_2_, baseline SGLT2 inhibitor use (yes/no), and study center. The MMRM was chosen because it uses all available longitudinal data and accounts for the correlation between repeated measurements within each subject, whereas ANCOVA would be limited to a single post-baseline time point and would not adequately handle the repeated-measure structure. Subject is included as a random effect (random intercept). The treatment effect will be reported as adjusted least-squares mean difference with 95% confidence intervals. Secondary endpoint analysis: Key secondary endpoints (including change in peak VO_2_ at week 12, NT-proBNP, 6-minute walk test, and NYHA functional class) will be analyzed using the same MMRM for continuous variables or logistic regression for categorical variables (with NYHA class dichotomized as improvement ≥1 grade vs. no improvement). To control type I error inflation due to multiplicity, a fixed-sequence testing procedure is prespecified: formal hypothesis testing for these four key secondary endpoints will proceed only if the primary endpoint (week 24 peak VO_2_) is statistically significant (*P* < 0.05), in the following order: ① week 12 peak VO_2_ change → ② NT-proBNP → ③ 6MWT → ④ NYHA class improvement (≥1 grade). All other secondary endpoints (including echocardiographic parameters, TCM syndrome score, individual symptoms/signs, EQ-5D, and coagulation function) are designated as exploratory/supportive endpoints, for which only descriptive statistics and unadjusted *P*-values will be reported; between-group comparisons for these exploratory endpoints will be performed using *t*-tests or Mann–Whitney *U* tests as appropriate, with unadjusted *P*-values provided for descriptive reference only, explicitly labelled as hypothesis-generating and not subject to formal inferential conclusions; hence, no multiplicity adjustment is applied to them. Center heterogeneity: Study center is included as a fixed effect in all MMRM models to account for potential variations in CPET execution, background care, and baseline characteristics across sites, ensuring robustness of the pooled treatment estimate.

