**Discussion:**

This study will evaluate the efficacy and safety of SXYX in treating HFpEF. The findings will provide a scientific basis for the clinical application of SXYX.

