### Sample size calculation

2.2

This study is a multicenter, randomized, double-blind, placebo-controlled trial. The primary outcome is a continuous variable. The allocation ratio between the SXYX group and the placebo group is 1:1. The sample size will be calculated using the formula for comparing two independent means. The formula is as follows:$$n_{1}=n_{2}=2{\left[\frac{(Z_{\alpha /2}+Z_{\beta })\sigma }{\delta }\right]}^{2}$$Based on preliminary data from a small-sample, exploratory pilot study, the peak oxygen consumption (VO_2_ peak) in patients with HFpEF after 6 months of treatment was 20.2 ± 4.8 mL/kg/min in those receiving Chinese herbal medicine, and 18.9 ± 4.2 mL/kg/min in those receiving standard conventional medical therapy. The standard deviations of 4.8 and 4.2 from the preliminary data were used solely to estimate the population standard deviation (*σ*). Based on the OptimEx-Clin Study (21), the latest prognostic studies of percentage of predicted peak VO_2_ in HFpEF (22), and the published results of traditional Chinese medicine for HFpEF with the Qi-deficiency and blood-stasis pattern (23), the minimal clinically important difference for sample size calculation was set at 2.7 mL/kg/min.$$\sigma^{2}=(S_{{}_{1}}^{2}+S_{2}^{2})/2=(4.8^{2}+4.2^{2})/2=20.34$$$$n_{1}=n_{2}=2{\left[\frac{(Z_{\alpha }+Z_{\beta })\sigma }{\delta }\right]}^{2}=2\left[\frac{{\left(1.96+1.282\right)}^{2}\times 20.34}{2.7^{2}}\right]\approx 59$$The calculation yielded approximately 59 patients per group. Accounting for an anticipated 20% dropout rate, the required sample size was adjusted to 74 patients per group, resulting in a total enrollment of 148 patients.

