#### Randomization

2.10.1

This study uses the central randomization system (Interactive Web Response System, IWRS) of The First Affiliated Hospital of Henan University of Chinese Medicine, employing stratified block randomization for enrollment. The study will be conducted at four TCM hospitals. Using study site as the stratification factor, patients will be randomly assigned in a 1:1 ratio to either the SXYX group or the placebo group (74 patients per group). The randomization list was generated by an independent statistician using the IWRS, producing randomization sequence numbers from 001 to 148, ensuring balanced sample sizes within each stratum. Randomization assignment will be implemented and managed using the EDC system (Electronic Data Capture) of the Evidence-Based Medicine Center of The First Affiliated Hospital of Henan University of Chinese Medicine. Investigators will obtain the investigational drug numbers for enrolled patients through this system. The IWRS is integrated with the EDC system in real time. The system automatically conceals the unallocated randomization sequence from the assignment results, thereby achieving allocation concealment.

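### Adverse events are compared between arms by significance test alone; effect estimates with 95% confidence intervals should be added, because the test has little power for uncommon harms at 74 per arm

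*Protocol article*

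**What the plan says.** The abstract's discussion states the aim: "This study will evaluate the efficacy and safety of SXYX in treating HFpEF". The introduction repeats it.

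Section 2.18 (Statistical analysis) defines "the safety set (SS), including all patients who received at least one dose of the study drug, used for safety analyses". Its one sentence on comparing adverse events between arms says that "comparisons of the incidence of adverse events between groups will also be performed using chi-square tests or Fisher's exact test". That sentence stands in the block on baseline and descriptive analyses. It names no effect measure, interval or bound.

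Elsewhere in 2.18 the primary treatment effect is to be given as an adjusted mean difference with a 95% confidence interval. P-values for the exploratory endpoints, which include coagulation, are to be marked as hypothesis-generating.

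Section 2.8 names the kinds of event expected to matter: hepatic or renal dysfunction, bleeding, allergy and gastrointestinal complaints. Section 2.2 sizes the trial on peak VO2 alone: "Accounting for an anticipated 20% dropout rate, the required sample size was adjusted to 74 patients per group". No expected adverse-event rate appears anywhere.

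**The concern.** A P-value alone does not tell a reader how much excess harm the data leave open. If events occur in a few percent of patients, a non-significant result is likely whether or not SXYX increases them. An interval would show that uncertainty; a bare test hides it.

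Within the article, an exploratory echocardiographic comparison carries a caution against over-reading, and the primary endpoint carries an interval. The adverse-event comparison carries neither. The risk of over-reading is not far-fetched: the introduction describes earlier studies of SXYX as having shown it to be safe, and in the same sentence calls their sample size insufficient.

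**Working it through.** **1. The plan's own sample size.** Inputs from section 2.2: "the minimal clinically important difference for sample size calculation was set at 2.7 mL/kg/min", a variance of 20.34, Z values of 1.96 and 1.282, and 20% dropout.

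n = 2 × (1.96 + 1.282)² × 20.34 / 2.7² = 58.65, rounded up to 59 per arm. Then 59 / (1 − 0.20) = 73.75, rounded up to 74. The stated figures are reproduced. No safety quantity enters.

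**2. Power of the adverse-event test.** Inputs: 74 per arm (section 2.10.1), which is the most the safety set can hold per arm; two-sided 0.05, which the article states for the primary endpoint and is assumed here for adverse events; event rates, all assumed. Method: for each of the 75 × 75 possible pairs of event counts, decide whether Fisher's exact test or the uncorrected chi-square test gives P < 0.05, then add up the binomial probabilities of the rejecting pairs.

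| Placebo vs SXYX (assumed) | Fisher | Chi-square |
|---|---|---|
| *Doubling* | | |
| 2% vs 4% | 2% | 9% |
| 5% vs 10% | 13% | 22% |
| 10% vs 20% | 32% | 41% |
| 15% vs 30% | 52% | 60% |
| 20% vs 40% | 71% | 77% |
| 25% vs 50% | 86% | 89% |
| *Tripling* | | |
| 2% vs 6% | 9% | 22% |
| 3% vs 9% | 20% | 34% |
| 5% vs 15% | 44% | 55% |
| 8% vs 24% | 71% | 78% |
| 10% vs 30% | 83% | 88% |

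**3. Where power passes 50%.** The normal approximation is Φ{(|p₁ − p₀|√n − 1.96√(2p̄(1 − p̄))) / √(p₁(1 − p₁) + p₀(1 − p₀))}, with p̄ the mean of the two rates. For 5% vs 15%: (0.10 × 8.602 − 1.96 × 0.4243) / 0.4183 = 0.07, so power is 0.53.

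Stepping through placebo rates, 50% is reached at about 13% for a doubling and about 5% for a tripling; 80% is reached at about 21.5% and 9%. Fisher's test is more conservative: the table puts its 50% point just below 15% for a doubling and between 5% and 8% for a tripling.

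**4. What an interval would add.** Suppose 8/74 on SXYX and 4/74 on placebo have an event.
- Fisher P = 0.37.
- Risk difference: 10.8% − 5.4% = 5.4 points; Newcombe 95% interval −3.9 to +15.1 points.
- Risk ratio 2.0; score 95% interval about 0.67 to 6.1.

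The result is non-significant, yet compatible with an excess of 15 points. With no events in 74 patients, the upper limit of the exact two-sided 95% interval is 1 − 0.025^(1/74) = 4.9%.

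**5. Could more patients solve it?** By the same approximation, 80% power needs 435 per arm for 5% vs 10%, 199 for 10% vs 20%, 141 for 5% vs 15% and 62 for 10% vs 30%. Only the last is within reach of 74 per arm.

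**The case against.** The strongest reply is that this is a condensed article without its analysis plan, and that intervals for adverse-event differences are commonly left to such a plan. Comparing incidence by chi-square or Fisher's test is standard, contradicts nothing in the article and does not prevent intervals from being reported. The sentence also sits among the descriptive analyses, apart from the hypothesis tests on endpoints. Much of this stands: a missing interval alone would be a weak point. What remains is that the article does choose a method for a stated aim, and chooses one less informative than the method it gives the primary endpoint in the same section.

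Three stronger readings should be resisted.

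- A reader might infer that a doubling or tripling of any harm would usually go undetected. The table does not support that. It depends on the background rate, which the article does not give, and common events such as any adverse event may well lie in the range where the test performs adequately.
- A reader might infer that the investigators will treat P > 0.05 as proof of safety. The article states no such rule.
- A reader might infer that the trial is too small, or that safety rests on one P-value. Low power for rare harm is ordinary at "the required sample size was adjusted to 74 patients per group, resulting in a total enrollment of 148 patients" and is not an error. Coagulation, which bears on bleeding, also gets between-group P-values, laboratory abnormalities are graded by CTCAE, and adverse events are coded in MedDRA.

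**Conclusion.** The point holds in a limited form. For adverse events the article fixes a significance test without an estimate, an interval or a caution on interpretation. For uncommon events that test says little: power is 9% / 22% (Fisher / chi-square) for 2% vs 6% and 13% / 22% for 5% vs 10%. A doubling is more likely missed than found only below about 13–15% placebo incidence, and a tripling only below about 5%, or somewhat above that with Fisher's test. Larger differences in common events are usually detected.

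These figures rest on assumed rates, a two-sided 0.05 level and 74 evaluable patients per arm. With 59 per arm, power for 5% vs 15% falls to 32% / 45%. This is an improvement in reporting that should be made; it is not a flaw in the design or the sample size.

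**What to change.** In section 2.18, for the safety set, report by arm the number and percentage with any adverse event, a serious adverse event, a treatment-related adverse event and each event type named in section 2.8. For each, give the risk difference with a 95% confidence interval (for example Newcombe), alongside the test or in place of it. Where an arm has no events, give the exact upper bound. Add one sentence saying that a non-significant comparison will not be taken as evidence of safety and that the safety conclusion will quote the upper confidence limit.

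If the test is kept, say that the interval leads, since the two can disagree: 12 vs 4 events of 74 gives Fisher P = 0.061 but a Newcombe interval of 0.6 to 21.4 points.

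The cost is a few lines of text and one table column. No patients, visits or data are added. The change does not improve detection of rare harm, and it will make the safety statement more cautious.
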